# *Bifidobacterium infantis* supplementation versus placebo in early life to improve immunity in infants exposed to HIV: a protocol for a randomized trial

**DOI:** 10.1186/s12906-023-04208-0

**Published:** 2023-10-18

**Keywords:** HIV exposure, South Africa, Live biotherapeutic, Randomised controlled trial, Bifidobacterium

## Abstract

**Introduction:**

Infants who are born from mothers with HIV (infants who are HIV exposed but uninfected; iHEU) are at higher risk of morbidity and display multiple immune alterations compared to infants who are HIV-unexposed (iHU). Easily implementable strategies to improve immunity of iHEU, and possibly subsequent clinical health outcomes, are needed. iHEU have altered gut microbiome composition and bifidobacterial depletion, and relative abundance of *Bifidobacterium infantis* has been associated with immune ontogeny, including humoral and cellular vaccine responses. Therefore, we will assess microbiological and immunological phenotypes and clinical outcomes in a randomized, double-blinded trial of *B. infantis* Rosell®-33 versus placebo given during the first month of life in South African iHEU.

**Methods:**

This is a parallel, randomised, controlled trial. Two-hundred breastfed iHEU will be enrolled from the Khayelitsha Site B Midwife Obstetric Unit in Cape Town, South Africa and 1:1 randomised to receive 8 × 10^9^ CFU *B. infantis* Rosell®-33 daily or placebo for the first 4 weeks of life, starting on day 1–3 of life. Infants will be followed over 36 weeks with extensive collection of meta-data and samples. Primary outcomes include gut microbiome composition and diversity, intestinal inflammation and microbial translocation and cellular vaccine responses. Additional outcomes include biological (e.g. gut metabolome and T cell phenotypes) and clinical (e.g. growth and morbidity) outcome measures.

**Discussion:**

The results of this trial will provide evidence whether *B. infantis* supplementation during early life could improve health outcomes for iHEU.

**Ethics and dissemination:**

Approval for this study has been obtained from the ethics committees at the University of Cape Town (HREC Ref 697/2022) and Seattle Children’s Research Institute (STUDY00003679).

## Background

Globally, it is estimated that 1.6 million infants are born annually to mothers living with HIV. While implementation of successful prevention programs has reduced rates of perinatal HIV acquisition to as low as 1% [1], risk of morbidity and mortality in sub-Saharan African infants who are exposed to HIV but uninfected (iHEU) is still higher compared to infants who are HIV-unexposed (iHU) [2–4], even when accounting for maternal health and socioeconomic factors [3]. Skin, mucous membrane, and respiratory tract infections are more common in iHEU [2, 4], suggesting a more vulnerable immunological state contributing to increased morbidity. We and others have shown that iHEU display multiple immune alterations compared to iHU [5–10]. Humoral vaccine responses are different from iHU [7, 9], and cellular immunity may also be altered in iHEU, including responses to Bacille Calmette Guerin (BCG), a live, attenuated *Mycobacterium bovis* vaccine [5, 8]. iHEU have elevated immune activation, including heightened T cell and monocyte activation [6] and elevated inflammatory cytokine responses [10]. In addition, in multiple settings iHEU have demonstrated impaired growth [11, 12], even after adjusting for gestational age at birth [11], and poorer neurodevelopment [13, 14]. Since iHEU make up over 15% of infants in some parts of the world [15], easily implementable strategies, ideally using readily available interventions, to improve immunity of iHEU and subsequent short-and longer-term health outcomes, are urgently needed.

Early-life colonization of the infant’s mucosal surfaces plays a pivotal role in maturation of the immune system [16, 17]. The infant gut is colonized with bacteria during and after delivery [18–20], and the community composition of iHEU gut microbiota is altered longitudinally compared to iHU [21–24], with iHEU having lower abundances of *Bifidobacteria* during early life [23]. This is not surprising as women with HIV have decreased *Bifidobacteria* in their gut [25], and maternal gut microbiota is a strong determinant of infant gut microbiota [26–28].

Emerging data suggest that the gut microbiota is related to mucosal vaccine responsiveness in infants [29–31]. Furthermore, Huda et al*.* found that CD4 + T cell stimulation index in response to intradermal BCG vaccine at 15 weeks of age positively correlated with *B. infantis* abundance at 6 weeks of age, and an earlier studies showed that breastfeeding at time of vaccination was correlated with better cell-mediated immune response to BCG vaccine [32–34]. These observational studies suggest that *Bifidobacterium* abundance, and possibly specifically *B. infantis*, around the time of vaccination may improve cellular vaccine responses; however, the observed correlations do not establish causality.

Several interventional trials have tested the effect of *B. infantis* on infant health, including for diarrhoea treatment and necrotizing enterocolitis prevention [35–37]. *B. infantis* supplementation has shown beneficial effects on enteric inflammation, mucin degradation, and antibiotic resistance gene carriage [38–40]. Few studies have examined the effect of *B. infantis* supplementation on adaptive immunity and so far, none of these studies included iHEU. Deficient *Bifidobacteriaceae* in the gut has been associated with expanded populations of neutrophils, basophils, plasmablasts, and memory CD8 + T cells in infant blood, indicating both innate and adaptive immune activation [41]. Conversely, infants with abundant gut *Bifidobacteriaceae* had higher frequency of anti-inflammatory non-classical monocytes and CD39 + Tregs [41], a highly suppressive Treg subset [42]. *B. infantis* supplementation was shown to silence intestinal Th2 (allergenic) and Th17 (autoimmune) responses in Scandinavian infants [41]. Importantly, 3 weeks of daily *B. infantis* supplementation from postnatal day 7 to 28 was sufficient to alter the gut microbiota up to one year of age in iHU [43]. This was true even in infants who received antibiotics after *B. infantis* supplementation was completed, which is important because the World Health Organization (WHO) currently recommends iHEU receive co-trimoxazole prophylaxis, commencing at 6 weeks of age and continued until 6 weeks post-breastfeeding cessation.

Collectively, these data form the basis of our hypothesis that supplementation with *B. infantis* in early life will lead to beneficial changes in gut microbiome composition and function, improved gut mucosal integrity and a more stable immune homeostasis, resulting in decreased immune activation and improved antigen-specific T cell immunity in iHEU. We will conduct a randomized, placebo-controlled, quadruple-blinded trial of *B. infantis* Rosell®-33 given during the first month of life in 200 breastfed iHEU with regular follow-up over nine months and biological and clinical outcomes.

## Methods and design

### Objectives

The primary objectives of this study are to evaluate the effect of early-life *B. infantis* Rosell®-33 supplementation in iHEU on gut microbiome composition and diversity (objective 1), and markers of intestinal inflammation and microbial translocation (objective 2) at 4 weeks of life, and the effect on Th1 cytokine responses to BCG at 7 weeks of life (objective 3).

The secondary objectives of this study are to evaluate the effect of *B. infantis* Rosell®-33 supplementation on longitudinal succession of the gut microbiota composition, diversity and function, stool metabolome and T cell subset ontogeny during the first 9 months of life.

Exploratory objectives are to evaluate whether *B. infantis* Rosell®-33 supplementation improves infant growth, vaccine responses (including antibody titres) to other early childhood vaccines, all-cause morbidity or neurodevelopment during the first 9 months of life.

### Trial design

This is a two-arm, randomized, double-blinded, placebo-controlled trial of *B. infantis* Rosell®-33 supplementation in the first 4 weeks of life in 200 breastfed iHEU. iHEU will be block-randomized in a 1:1 ratio to receive ~ 8 × 10^9^ CFU of *B. infantis* Rosell®-33 versus placebo daily from postpartum day 3 to 28. Participants will be followed over 9 months. Assessment of infant outcomes and sample collection will be done at birth, day 10–14 and weeks 4, 7, 15, 24 and 36 of life (Table 1).

**Table 1 Tab1:**
[figure not shown]
Schedule of enrolment, interventions and assessments

### Sample size

We propose to enrol 200 iHEU based on sample size calculation conducted for each of the three primary objectives.Objective 1: Sample size calculations were based on metagenomic data from D’Souza et al. (2020) [44], and on *B. infantis* copies in the stool collected at day 4–7 of life from infants in our current observational cohort from the same clinical site, where the mean *B. infantis* copy number was 3000 per 2.5 ng gDNA. The power analysis was based on a generalized linear regression approach, with a betabinomial error model for the dependent variable where varying effect sizes were injected to calculate effective power. The sample size of 100 iHEU per group is adequately powered to detect a difference of at least twofold for differential abundance testing and R^2^ values of 0.01 or higher in PERMANOVA analyses between iHEU administering *B. infanti*s Rosell®-33 versus those administering placebo, even after accounting for a lost-to-follow-up rate of 9% at week 36 (based on our observational cohort).Objective 2: Based on data from our observational cohort where the mean log intestinal fatty-acid binding protein (iFABP) plasma concentration in iHEU at day 4–7 was 0.454 ng/ml with a standard deviation of 0.164, we will have 80% power to detect a 20% difference in iFABP with *n* = 51 per group. Therefore, our proposed sample size of *n* = 100 per group will be ample to detect what we think is a meaningful difference.Objective 3: A sample size of 78 per group (total *n* = 156) will provide 80% power to detect a 45% increase in total net Th1 cytokine responses to BCG based on preliminary data in iHEU where the mean response was 0.78 and standard deviation 0.8, and the proposed sample size of 100 iHEU per arm accounts for a predicted loss-to-follow-up rate of 2.5% to 7 weeks, resulting in an expected sample size of *n* = 195 at week 7.

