### Outcomes and statistical methods

#### Primary outcomes

Analyses will follow intention-to-treat (ITT) principles comparing the two randomised groups.We will compare Alpha (Shannon) and Beta (Bray Curtis and UniFrac) diversity metrics, calculated from shotgun metagenomic sequencing data for each infant stool sample, between treatment arms at 4 weeks. Cross-sectional abundance differences for taxa and functional genes will be assessed using DeSeq2 (negative-binomial) [50] or Corncob (beta-binomial) [51] regression models, with the Benjamini–Hochberg multiple-test correction on the resulting *p*-values (to control the false-discovery-rate (FDR)) [52]. Regressions will be adjusted for confounders, like sex, weight, and feeding mode.Markers of intestinal inflammation and microbial translocation at baseline, weeks 4, 7 and 36: We will compare markers of intestinal inflammation and microbial translocation (Lipocalin-2 (Lcn-2), soluble CD163 (sCD163), iFABP and lipopolysaccharide binding protein (LBP) measured by ELISA in infant plasma) cross-sectionally at each time point between groups using Mann–Whitney U tests. We will correlate absolute concentrations of *B. infantis* in the fecal microbiome with these markers. We will use a mixed-effects regression (MER) modeling approach to account for repeated measurements and for relevant covariates like feeding status and sex.BCG-specific total net Th1 cytokine producing cells at 7 weeks of life: We will compare frequencies of total net cytokine producing cells in response to stimulation with BCG between arms at weeks 7 using linear regression after adjusting for confounders, like sex, weight, and feeding mode. Additionally, T cell response data will be analyzed by COMPASS [53] to compute a ‘functionality score’ or ‘polyfunctionality score’. This analysis will be a regression model testing the association between functionality or polyfunctionality scores and iHEU (*B. infantis* versus placebo). We will perform two-sided hypothesis testing with alpha = 0.05. If the model shows a significant result (*p* < 0.05), we will perform a series of univariate analyses in which we test for an association between a particular functional profile and arm. Those profiles identified as significantly associated will be incorporated into a multivariate linear regression model, which will include two-way interaction terms. This will allow us to create a model that includes the cytokine-producing profiles that are most associated with the intervention. We will test the classification accuracy of this model using receiver-operative curve (ROC) analysis. In all models, we will include sex, birth weight, and feeding mode as possible confounders.

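### The iFABP sample size (51 per group) is for 20% of a log mean, not a 20% difference in iFABP; the BCG figure (78 per group) does not reproduce from its printed inputs. Both need restating; enrolment does not change

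*Protocol article*

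**What the plan says.** All the figures are in the Sample size section of the protocol article.

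- **Objective 2 (iFABP).** The mean log plasma concentration at day 4–7 in the observational cohort "was 0.454 ng/ml with a standard deviation of 0.164". From this the article concludes that "we will have 80% power to detect a 20% difference in iFABP with" 51 per group, and calls 100 per group ample. The base of the logarithm is not given.
- **Objective 3 (BCG Th1 response).** "A sample size of 78 per group" (156 in total) "will provide 80% power to detect a 45% increase in total net Th1 cytokine responses to BCG", from preliminary data "where the mean response was 0.78 and standard deviation 0.8". The proposed 100 per arm "accounts for a predicted loss-to-follow-up rate of 2.5% to 7 weeks", leaving 195 infants at week 7.

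The section gives no alpha. The Primary outcomes section says, within the T-cell analysis: "We will perform two-sided hypothesis testing with alpha = 0.05". Under Trial design, "iHEU will be block-randomized in a 1:1 ratio".

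**The concern.** Each statement ties a sample size to a named effect, and that effect is what readers will use to judge a null result on a primary objective.

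For iFABP, the mean and SD are described as log-scale values but the effect is described as a percentage of iFABP. A percentage of a log mean is not a percentage of the concentration, and what it amounts to depends on the base. If the effect size was worked out on one scale and described on the other, the stated detectable difference could be wrong by a factor of about two.

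For BCG, 45% of 0.78 divided by 0.8 is a little under 0.45 SD, so 78 per group looks slightly too few for the printed inputs.

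**Working it through.** **Inputs.** Two-sided alpha 0.05 (Primary outcomes), 80% power, 1:1 allocation (Trial design); means, SDs and effects from Sample size.

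**Formulas.** n per group = 2(1.960 + 0.8416)² / d² = 15.70 / d², where d = difference / SD. Power = Φ(d√(n/2) − 1.960). An exact t-test is quoted where it differs.

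**Objective 2: reproducing 51.** Take 20% of the log mean: 0.2 × 0.454 = 0.0908. Then d = 0.0908 / 0.164 = 0.554 and n = 15.70 / 0.3065 = 51.2 (t-test 52.2). Power at 51 is 79.8% (t-test 79.1%). The stated figure is therefore recovered, to within rounding, by applying the 20% to the log mean.

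**What 0.0908 log units means in iFABP.**

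- log10: 10^0.0908 = 1.233 and 10^−0.0908 = 0.811, that is +23% or −19%.
- natural log: e^0.0908 = 1.095 and e^−0.0908 = 0.913, that is +9.5% or −8.7%.

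**What a true 20% change would need (SD 0.164 on the log scale).**

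| Base | Change | Log difference | d | n per group | Power at 51 |
|---|---|---|---|---|---|
| log10 | ×1.2 | 0.0792 | 0.483 | 67.3, so 68 | 68% |
| log10 | ×0.8 | 0.0969 | 0.591 | 45.0, so 45 | 85% |
| natural | ×1.2 | 0.1823 | 1.112 | 12.7, so 13 | above 99% |
| natural | ×0.8 | 0.2231 | 1.361 | 8.5, so 9 | above 99% |

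None of these is 51.

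**Objective 2 at the planned size.** I assume about 97 per group. This borrows the week-7 retention (200 × 0.975 = 195) for the week-4 endpoint, for which the article gives no figure. The difference detectable with 80% power is 0.164 × 2.8016 × √(2/97) = 0.0660 log units. That is a ratio of 1.16 or 0.86 on log10, or 1.07 or 0.94 on natural log. The least favourable case, a true 20% rise on log10, has power Φ(0.483 × 6.964 − 1.960) = Φ(1.40) = 92%.

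**Objective 3: the printed inputs.** Difference = 0.45 × 0.78 = 0.351; d = 0.351 / 0.8 = 0.439; n = 15.70 / 0.1925 = 81.5, so 82 (t-test 82.5, so 83). Power at 78 = Φ(0.439 × 6.245 − 1.960) = Φ(0.78) = 78.2% (t-test 77.7%). One-sided alpha 0.05 gives 65, so it does not explain 78.

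**What would give 78.** d = 0.45 gives 15.70 / 0.2025 = 77.5, so 78. That d arises in at least two ways:

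- an SD of 0.78, which prints as 0.8: 0.351 / 0.78 = 0.45;
- a difference of 0.36 with SD 0.8, which is a 0.36 / 0.78 = 46% increase.

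Over the range of SDs that print as 0.8 (0.75 to 0.85), n runs from about 72 to 93.

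**Objective 3 at the expected 195.** With 97 per group and a common SD of 0.8, power for a 45% increase is Φ(0.439 × 6.964 − 1.960) = Φ(1.10) = 86%. The increase detectable with 80% power is 0.8 × 2.8016 × √(2/97) / 0.78 = 0.322 / 0.78 = 41%.

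**The case against.** **The mismatch may be small.** On log10 the shift is +23% or −19%, near enough to 20% for planning. On natural log the plan understates its own sensitivity. Both remarks are right, but the article does not say which base applies, so a reader cannot tell whether the detectable change is about 9% or about 23%.

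**The word log may be a slip.** The mean carries a unit of ng/ml. If 0.454 and 0.164 were raw concentrations, 51 would be right for a 20% difference. The article does call it a mean log concentration, however, so the sentence needs correcting either way.

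**The BCG gap may be rounding.** This largely stands. The SD is printed to one decimal, and 0.78 gives exactly 78. The planned covariate adjustment could also close the gap: if covariates explained 5% of the variance (an assumption), 81.5 × 0.95 = 77.5. Even at SD 0.8 exactly, the shortfall is about 2 points of power.

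**Stronger readings.** A reader might infer three things that the documents do not support.

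- That 78 is simply wrong, or that the 45% was a standardised effect misread as a percentage. Rounding of the SD explains 78 equally well.
- That BCG power is much lower, because an SD close to the mean suggests skew and a proportional rise would raise the treated-arm SD. The article states neither a rising SD nor a raw-scale analysis of skewed data. A net response may fall below zero if it is background-subtracted, and any transformation may be left to the analysis plan.
- That the trial is too small. The working shows otherwise for both objectives.

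**Conclusion.** The iFABP statement is wrong as written. With the log-scale mean and SD that the article gives, 51 per group has 80% power for a shift of 0.0908 log units, which is not a 20% difference in iFABP on log10 or on natural log. The error is modest on log10 and about twofold on natural log.

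The BCG statement is a lesser matter. It does not reproduce from the printed inputs (82 to 83 per group, not 78; about 78% power, not 80%), but it is consistent with an unrounded SD of about 0.78.

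Neither point touches the design. The conclusion that 100 per arm is sufficient for these two objectives stands, with about 86% power for the 45% BCG increase and about 92% or more for a true 20% iFABP change. This rests on two-sided alpha 0.05, a common SD in the two arms, a normal approximation for iFABP (the planned Mann–Whitney test would cost little) and, for Objective 2, week-7 retention taken as an assumption for week 4.

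**What to change.** **Objective 2.** State the log base and give the detectable effect as a ratio. For log10: 51 per group has 80% power for a ratio of about 1.23 or 0.81, and about 97 per group for about 1.16 or 0.86. For natural log the pairs are 1.10 or 0.91, and 1.07 or 0.94. Say that the 97 assumes week-7 retention at week 4. If the values turn out to be raw concentrations, remove the word log instead.

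**Objective 3.** Print the SD to two decimals. If it is 0.78, the present sentence stands. If it is 0.80, restate it as 78 per group for 0.45 SD, about a 46% increase. With a common SD of 0.8, add that the expected 195 infants give about 86% power for a 45% increase and 80% power for about 41%; recompute these if the SD differs.

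**Cost.** A few words in one section. Enrolment, visits and analyses are unchanged.

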### Participants, intervention and outcomes

#### Study setting and recruitment

Mothers and infants will be recruited from the Khayelitsha (Site B) Midwife Obstetrics Unit in Cape Town, South Africa. Study staff will present information about the trial to all mothers in the waiting room of the antenatal clinic to sensitize women about the study prior to delivery. Identification of potential study participants will occur in the delivery ward. Routine Midwife Obstetrics Unit staff will alert study staff of an potential participant to approach. Those who could be eligible for the study and are interested will provide informed consent. Women will then be screened to confirm eligibility, and eligible participants will be enrolled in the study.

#### Eligibility criteria mother and infant

Maternal eligibility criteria are:Willing and able to provide signed and dated informed consent form18 years of age or olderDocumented HIV seropositive and antiretroviral therapy initiated before the third trimester of pregnancyPlanning on exclusively breastfeedingPlanning on remaining in Cape Town until 9 months postpartumNo severe illnesses, e.g. current tuberculosis (TB) or known household TB contactNo eclampsia, or chronic disorder or medications (other than antiretrovirals and cotrimoxazole prophylaxis) that in the opinion of the investigator could alter immunity

Infant eligibility criteria are:Documented HIV seronegative at birthBorn at term (completed at least 37 weeks of gestation), without pregnancy or delivery complications including birth asphyxia, seizures, sepsis, major congenital anomalies or congenital infectionsBirth weight > 2.4kgsNo known contraindications to components of the interventional productsNot taking additional probiotics or prebioticsAny condition that in the opinion of the investigator would make participation in the trial unsafe or otherwise interfere with the aims of the trial.

### Informed consent

Consent is performed by a trained study nurse or counsellor. Per South African Good Clinical Practice (GCP) guidelines, the mother’s literacy will be assessed, and study staff will assess basic understanding of the trial by asking her to repeat some of the information about the study. The mother will be consented in whichever language she feels most comfortable, isiXhosa or English, and consent forms will be available in either language. For illiterate participants, an impartial witness will sign to testify that the participant understood the consent.

### Intervention

The investigational product is *B. infantis* Rosell®-33, one of the three bacterial strains composing the commercial infant formula Probiokid®. The Food and Drug Administration (FDA) has classified these three strains, including *B. infantis* Rosell®-33, individually or as a blend, with the Generally Recognized as Safe status (GRAS notice 758, 2018), and clinical studies have shown the safety for use in infants younger than six months [45–47]. The formula has shown beneficial effects in children on immune maturation, anaemia, and reduction of common infections like diarrhoea and respiratory tract infections, as reviewed elsewhere [48]. Beneficial effects include long-term restructuring of the infant gut microbiota, an increased fecal anti-inflammatory signature, and significantly higher levels of stool and salivary sIgA [45–47]. As such, the strain alone has been already studied in a randomized, double-blind, placebo-controlled study, where *B. infantis* Rosell®-33 was deemed safe and well tolerated in 221 healthy, three- to twelve-months-old infants [46]. A post-hoc analysis based on a sample of infants from the Manzano 2017 study showed *B. infantis* Rosell®-33 maintained a infant-like microbiome profile rich in bacteria able to digest lactose such as *Bifidobacteria*, regardless of any influencing factors such as diet and birth mode [45]. In contrast, in the placebo group, there was significant increase in common constituents of healthy adult gut microbiota, and fewer *Bifidobacteria* (most specifically *Bifidobacterium bifidum* and *Bifidobacterium breve*).

Health Canada has recognized that *Bifidobacterium infantis* Rosell®-33 can help formula-fed babies develop a similar microbiota as to breast-fed infants.

For this trial, Lallemand Health Solutions will manufacture the investigational product containing 8 × 10^9^ CFU *B. infantis* Rosell®-33 per dose (single microbial active ingredient) and carrier material (maltodextrin), as well as the placebo (containing all materials besides *B. infantis* Rosell®-33). Mothers will be provided with two 14-day supplies of identical looking 1 g sachets containing either *B. infantis* Rosell®-33 or the placebo powder at enrolment and the first follow-up visit, both of which can be stored at room temperature. Mothers will be requested to pour one sachet (containing the investigational product or placebo) into a provided sterile cup daily, add 2 mL of expressed breastmilk, mix the powder and breastmilk, and then cup-feed her infant immediately. If, for any reason, the mother is unable to produce any/enough breastmilk during the intervention phase and is therefore using infant formula, she will be advised to mix the sachet with formula.

